#### Imaging data analysis.

MRI preprocessing and statistical analyses of all images will be implemented on MATLAB2021b (https://ww2.mathworks.cn) using statistical parametric mapping software (SPM12, https://www.fil.ion.ucl.ac.uk/spm/software/spm12/).

The processed data from DTI, rs-fMRI, and ASL will be employed to evaluate cerebellar stimulation’s effect on aphasia recovery in terms of structure, function, and perfusion. For the DTI data, variations in the cerebral-cerebellar loop’s structure will be identified between different groups and pre-/post treatment using Tract-Based Spatial Statistics (TBSS) analysis. With rs-fMRI, the analysis of amplitude of low-frequency fluctuations (ALFF), regional homogeneity (ReHo), and functional connectivity density (FCD) will be completed to assess the local and global functional connectivity inside the language networks. Using ASL sequences, the cerebral perfusion for every participant will be calculated, targeting the perfusion alteration, particularly the lesion area. One-way ANOVA will be performed to compare the imaging parameters among the groups (pre-vs. post-treatment, real vs. sham treatment). A linear regression analysis will be applied to establish the relationship between behavioral performance and the parameters. Any differences among these conditions are regarded as significant when the P-value is < 0.05 at the voxel level, with an FDR cluster-corrected P-value < 0.05 (two-tailed).

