**Methods:**

Our study will recruit sixty-six PSA patients, who will be randomly divided into either a real or a sham rTMS group with equal distribution. The real rTMS group (n  =  33) will receive rTMS treatment over the right cerebellar hemisphere along with speech-language therapy (SLT), while the sham group (n  =  33) will receive sham stimulation and SLT. We will assess the outcomes at five intervals: before rTMS treatment, 2, 12, and 24 weeks, and 1-year post-treatment. The primary outcome in this research is the change in performance of the West Aphasia Battery from baseline to the final follow-up. Secondary outcomes include alterations in the structure, function, and perfusion neuroimaging data, as well as changes in non-verbal cognitive functions, measured using the Loewenstein Occupational Therapy Cognitive Assessment over time and between the groups. Any adverse event related to rTMS therapy will also be recorded. The results of this trial will provide insights into whether cerebellar rTMS stimulation (1) improves language function recovery in subacute phase PSA patients; (2) strengthens the functional connection of the cerebro-cerebellar network, and (3) enhances aphasia treatment outcomes by improving non-linguistic cognitive functions. We commenced patient recruitment for this trial in June 2026, and it is currently in progress.

**Registration** This project was prospectively registered at the Chinese Clinical Trial Registry (ChiCTR2600125453).

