The majority of prior research, however, has focused on chronic stroke phase aphasia patients whose functional brain structures have already undergone irreversible alterations [4,33,34]. This could potentially explain the observed lack of significant effects of cerebellar NIBS on language recovery [22,35]. Recent guidelines indicate the safe and tolerable application of NIBS even in the sub-acute phase, with no severe adverse effects reported [36–39]. The current study protocol proposes to stimulate the right cerebellum with repetitive transcranial magnetic stimulation (rTMS) in order to enhance SLT for PSA patients in the sub-acute phase. The study’s primary objective is to assess the short- and long-term efficacy of cerebellar rTMS for aphasia recovery in these patients under a randomized, sham-controlled design. The secondary purpose is to examine alterations in functional connectivity between the cerebellum and language-related cortical regions pre- and post-treatment and elucidate the neural restructuring mechanism. Moreover, from a neuropsychological perspective, the study will investigate whether cerebellar stimulation can improve language symptoms through enhancing non-linguistic cognitive functions.

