#### Secondary outcome measurements.

All participants will undergo head MRI scans using a 3.0T, 48-channel MRI scanner (GE Healthcare, USA). T1-weighted sequences, T2-weighted sequences, and T2-fluid attenuated inversion recovery (FLAIR) will be obtained to identify and extract lesions. Resting-state functional MRI (rs-fMRI) will be conducted to evaluate local and global functional connectivity networks associated with language function enhancement. Moreover, diffusion tensor imaging (DTI) and Arterial Spin Labeling (ASL) sequences will be utilized to investigate changes in brain fibers and cerebral blood flow related to cerebellar stimulation on PSA, respectively. During the scanning procedure, rubber earplugs will be used to reduce noise, and foam pads will be utilized to secure the head position and minimize motion artifacts. In the rs-fMRI scanning session, participants will be instructed to close their eyes and remain awake.

In addition, the Loewenstein Occupational Therapy Cognitive Assessment (LOTCA) will be used to measure nonverbal cognitive function, encompassing domains of orientation, visual perception, spatial perception, motor praxis, visuo-motor organization, thinking operations and attention [47–48]. The total score ranges from 26 to 115 (the attention score was computed separately, ranging from 1 to 4). A lower score signifies more severe cognitive deficits.

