### Expected conclusions

(1) Following treatment, language and non-verbal cognitive functions in the rTMS group are expected to exhibit better performance compared to those in the sham group.(2) Changes in spontaneous neural activity within the fronto-thalamic-cerebellar circuit and enhancement in perfusion within the lesion site are anticipated following the stimulation therapy.

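### The rs-fMRI measures named in the imaging analysis do not isolate the cerebellum-to-language-cortex connectivity that the secondary objective is about

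*Protocol article*

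**What the plan says.** **The aim.** The last paragraph of the Introduction states: "The secondary purpose is to examine alterations in functional connectivity between the cerebellum and language-related cortical regions pre- and post-treatment". The Abstract (Methods) asks, as the second of three questions, whether cerebellar rTMS "strengthens the functional connection of the cerebro-cerebellar network".

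**The measures.** Under Secondary outcome measurements, rs-fMRI is acquired to "evaluate local and global functional connectivity networks associated with language function enhancement". Imaging data analysis then names the measures: "With rs-fMRI, the analysis of amplitude of low-frequency fluctuations (ALFF), regional homogeneity (ReHo), and functional connectivity density (FCD) will be completed". The end of the same sentence gives their target: "functional connectivity density (FCD) will be completed to assess the local and global functional connectivity inside the language networks". The article does not define these networks. For DTI, variations in the cerebral-cerebellar "loop’s structure will be identified between different groups and pre-/post treatment using Tract-Based Spatial Statistics (TBSS) analysis". ASL is used for perfusion.

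**The expected result.** Expected conclusions anticipates "Changes in spontaneous neural activity within the fronto-thalamic-cerebellar circuit", which describes activity rather than coupling between regions.

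No seed-based, ROI-to-ROI or other cerebellum-to-cortex functional connectivity measure is named anywhere in the article.

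**The concern.** The objective concerns a pair of distant regions: does the coupling between the stimulated cerebellum and the language cortex change, and does it change more with real than with sham stimulation? A measure that answers this must have both ends of the connection in its definition. The article does name its rs-fMRI measures, and none of them has that property.

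If the list is followed as written, the trial will have maps of local activity, local synchrony and connection counts, but no variable for the link itself. A real gain in coupling could go unseen, or appear only as a higher count that cannot be traced to the cerebellum. A report that stimulation strengthened the cerebro-cerebellar connection would then be an inference from indirect measures. If a seed and targets were chosen only after the data had been examined, that statement would be weakened further.

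**Working it through.** The plan gives no figure on this point, so there is none to reproduce. The check sets the objective against each named analysis, using the usual meanings of the measures, which the article does not spell out.

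| Named analysis | What it quantifies | Does it give cerebellum-to-cortex functional coupling? |
|---|---|---|
| ALFF | Signal amplitude at one voxel | No; one location only |
| ReHo | Synchrony of a voxel with its neighbours | No; local by definition |
| FCD | Number of voxels to which a voxel is connected | Not specifically; the partner is not identified |
| TBSS on DTI | White-matter structure | No; it covers the loop, but structurally |
| ASL | Perfusion | No |

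**Illustration with assumed data.** Nothing here comes from the trial. Assume 50 language voxels sharing one signal, 10 cerebellar voxels sharing another, and 450 unrelated voxels. The shared signal carries 0.6 of each voxel's variance. A connection is counted when a correlation exceeds 0.25. Let r be the true correlation between the two shared signals.

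- Two language voxels correlate at 0.6 whatever r is, so each has 49 connections within the language set.
- A language voxel and a cerebellar voxel correlate at 0.6 × r, which is 0.06, 0.18 and 0.36 for r = 0.1, 0.3 and 0.6. Only 0.36 passes the threshold. The crossing is at r = 0.25 / 0.6 = 0.417.
- The two regional mean signals correlate at 0.6r / √[(0.6 + 0.4/50)(0.6 + 0.4/10)] = 0.6r / √(0.608 × 0.640) = 0.962r, which is 0.10, 0.29 and 0.58.

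A simulation of this set-up with 20,000 time points gave:

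| True r | Amplitude (SD) in language voxels | Connections within language set | Connections over all voxels | ROI-to-ROI correlation |
|---|---|---|---|---|
| 0.1 | 0.996 | 49.0 | 49.0 | 0.104 |
| 0.3 | 1.004 | 49.0 | 49.0 | 0.294 |
| 0.6 | 0.999 | 49.0 | 59.0 | 0.575 |

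The ROI-to-ROI measure follows r throughout. Amplitude does not move, and neither does the count within the language set. ReHo was not simulated, but the correlation between language voxels is fixed at 0.6 here, so synchrony among them does not depend on r.

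The all-voxel count does respond. It rises by 59 − 49 = 10, exactly the 10 cerebellar voxels, but only once the threshold is passed. Any other 10 voxels gaining a connection would give the same rise. If the language network were defined to include the cerebellum, the count inside it would behave like the all-voxel column. So FCD is not blind to the link, but it is non-specific and depends on the threshold.

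**The case against.** Several points on the other side have force.

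- **The list may not be closed.** The article does not say that ALFF, ReHo and FCD are the only measures, and it condenses a longer protocol in which seeds and ROIs could be set out. It is true that the text does not call the list exhaustive, and this write-up does not claim that. But the article goes beyond silence: it selects measures, gives them a target, and they do not match the objective it states.
- **FCD is a connectivity measure.** Global FCD can respond to new long-range connections, and the language network is not defined as cortical only. The Introduction itself credits the right cerebellum with language functions. This stands, and it is why the point is about lack of specificity. FCD still does not say which region gained the connection.
- **The broadly worded outcomes are covered.** The secondary imaging outcome is framed as structure, function and perfusion, each of which has an analysis, and ALFF suits the spontaneous activity named in Expected conclusions. This is correct, but it leaves the connectivity objective and the Abstract's second question without a direct measure.

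Two stronger readings are tempting, and the documents do not support them. A reader might infer that the second question cannot be answered at all. It can: the rs-fMRI scans are planned, so the gap lies in the listed analyses and not in the data. A reader might also argue that changes in ALFF, ReHo or FCD would merely reflect recovery around the lesion in both arms. The randomised comparison with sham deals with recovery common to both arms, and seed-based connectivity would be exposed to it equally, so that argument does not separate the planned measures from the proposed one.

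**Conclusion.** The point holds in limited form. None of the three named rs-fMRI measures specifically isolates functional connectivity between the cerebellum and language-related cortex, and the only analysis tied to the cerebral-cerebellar loop is structural. The analyses as listed cannot directly support an affirmative answer to the second of the Abstract's three questions.

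This should be corrected, but its reach is modest: one secondary, mechanistic aim. The primary WAB outcome, the sample size and the safety outcomes do not depend on it. The conclusion rests on the usual definitions of ALFF, ReHo and FCD, and on taking the named measures as the ones planned. It does not rest on the simulation, whose voxel numbers, shared variance and threshold are assumed and which only illustrates the behaviour.

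**What to change.** Under Imaging data analysis, add one prespecified seed-based or ROI-to-ROI functional connectivity measure from the stimulated right cerebellar region to named language cortical regions. State that its change from baseline will be compared between real and sham, and that the answer to the Abstract's second question will be based on this comparison. Fix the seed, the target regions and the follow-up time point or points, chosen from those already planned, before the imaging data are examined.

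ALFF, ReHo and FCD can stay as complementary measures; nothing here requires removing them.

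The cost is a few sentences in the plan and a little extra processing of rs-fMRI scans already being collected. No additional scans or patients are needed. Trial status gives December 31, 2028 for the end of recruitment and June 1, 2029 for the end of data collection, so the change can be made well before analysis.

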## Introduction

Post-stroke aphasia (PSA), often results from brain lesions impacting cortical and subcortical structures, is characterized by difficulties in speech, comprehension, repetition, and naming, leading to extended hospital stays, diminished quality of life, and increased mortality [1]. Currently, the go-to treatment protocol for PSA is speech-language therapy (SLT), which has demonstrated beneficial effects on language function [2–4]. However, not all PSA patients have access to this therapy, and not all benefit from it. Despite SLT, individuals with aphasia frequently experience persistent communication challenges [3,5]. Thus, the development of additional, more effective therapeutic approaches for aphasia treatment is crucial. Researchers are exploring non-invasive brain stimulation (NIBS), a safe, painless, and cost-effective technique, as a potential enhancer for aphasia treatment [6–8]. The combination of NIBS with traditional therapy shows promise in aphasia recovery, as underscored by international guidelines [6,8].

Aphasia rehabilitation often targets the cerebrum, with most research focusing on stimulation of the left hemisphere due to the reactivation and utilization of the residual left-hemisphere tissue in language recovery [6,8–10]. Some studies apply inhibitory stimulation to the right hemisphere, based on the theory of inter-hemispheric disinhibition [11–13]. However, there are limitations to both approaches over the cerebral hemispheres [14]. Stimulating the left cerebral hemisphere can be problematic, as stroke often leaves areas with low electrical resistance due to filled with cerebrospinal fluid. This reduces the stimulation exposure on the targeted tissue [15–16]. Conversely, inhibiting the right hemisphere might also have negative effects, as evidence suggests that it may play a compensatory role in recovering language functions after a stroke [17–18]. Given the variability in lesion location and size, as well as the unpredictable brain reorganization, determining the optimal stimulation strategy at the cortical level is challenging [19]. Hence, it’s crucial to develop novel stimulation protocols targeting other significant areas involved in language processing, thereby improving the effectiveness of PSA treatment.

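### Perfusion change within the lesion is a named target, but the only significance rule stated for imaging works voxel by voxel and does not measure change in each patient's own lesion

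*Protocol article*

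**What the plan says.** Three places in the protocol article single out perfusion in the lesion.

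- **Imaging data analysis:** perfusion is calculated for every participant from ASL, "targeting the perfusion alteration, particularly the lesion area".
- **Trial innovation:** the lesion is again the part of particular interest when changes after treatment are gauged.
- **Expected conclusions:** "enhancement in perfusion within the lesion site are anticipated following the stimulation therapy".

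For group comparison, Imaging data analysis names SPM12 and then says: "One-way ANOVA will be performed to compare the imaging parameters among the groups". The comparisons are pre versus post and real versus sham. The significance rule that follows is general: "Any differences among these conditions are regarded as significant when the P-value is < 0.05 at the voxel level", with an FDR cluster-corrected P below 0.05, two-tailed. The linear regression in the same section relates imaging parameters to behaviour. It does not test a treatment effect on perfusion.

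The inclusion criteria require the lesion to be in the left cerebral hemisphere and set no further limit on its location. The section on secondary outcome measurements says that the structural sequences "will be obtained to identify and extract lesions". No section links the extracted lesion to the perfusion comparison.

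**The concern.** A voxelwise test asks whether perfusion at one location in a common space differs between groups. The lesion site is not one location: it differs from patient to patient. This has two consequences.

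1. **What is estimated.** At any voxel, some patients contribute lesioned tissue and others intact tissue. The group difference there is an average over both. A significant cluster would not by itself show that perfusion rose inside lesions, because patients with intact tissue at that place also contribute to it. This holds whatever the power.
2. **Sensitivity.** If stimulation raises perfusion mainly inside the lesion, the effect at a voxel is diluted by the share of patients whose lesion covers that voxel.

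At stake is whether the anticipated finding on lesion perfusion can be supported or refuted by the analysis as written. A second risk is that, with no lesion measure stated in advance, the choice between a voxel map and a regional value could be made after both have been seen.

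**Working it through.** **The plan's own figure first.** The Sample size section gives d = 0.86, two-sided alpha 0.05, power 90%, and 30 per arm. For a two-sample t-test with n per arm, df = 2n − 2 and the non-centrality is δ = d × √(n/2).

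- n = 29: δ = 0.86 × √14.5 = 3.27, power 0.896.
- n = 30: δ = 0.86 × √15 = 3.33, power 0.906.

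So 30 per arm reproduces. That figure is for language function. The article gives none for perfusion.

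**Inputs for the illustration**

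- 30 per arm, from the Sample size section.
- Effect inside the patient's own lesion: d = 0.8 (assumption).
- Effect outside the lesion: zero (assumption).
- Overlap f, the share of patients whose lesion covers a given voxel (assumption, shown as a range).
- The same standard deviation for a voxel value as for a mask mean (assumption).

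**Formula.** Effect at the voxel = f × 0.8. Then δ = (f × 0.8) × √15, df = 58, two-sided critical value 2.002, and power from the non-central t distribution.

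| Measure | Effect d | δ | Power at 0.05 |
|---|---|---|---|
| Mean over own lesion mask | 0.80 | 3.10 | 0.86 |
| Voxel, f = 80% | 0.64 | 2.48 | 0.68 |
| Voxel, f = 70% | 0.56 | 2.17 | 0.57 |
| Voxel, f = 50% | 0.40 | 1.55 | 0.33 |
| Voxel, f = 30% | 0.24 | 0.93 | 0.15 |
| Voxel, f = 20% | 0.16 | 0.62 | 0.09 |

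The voxel rows are for one voxel without cluster correction.

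**Check with another effect size.** With d = 0.86 borrowed from the primary outcome, and allowing for the extra spread when only some treated patients respond at the voxel, power is 0.91 for the mask mean. At a voxel it is 0.35, 0.16 and 0.10 for f = 50%, 30% and 20%. Simulation with 40,000 runs gave 0.349, 0.160 and 0.097. The pattern is the same.

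**Check on the zero effect outside.** Suppose instead an effect of 0.4 outside the lesion (assumption) and f = 50%. The voxel effect is 0.5 × 0.8 + 0.5 × 0.4 = 0.60, δ = 2.32, power 0.63. The loss shrinks, but a positive voxel then says even less about the lesion itself.

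**The case against.** The best reply is that a regional lesion analysis may already be intended. Perfusion is to be calculated for every participant with emphasis on the lesion, lesions are to be extracted, and the ANOVA sentence speaks of imaging parameters without saying that they are voxel values. The voxel and cluster threshold might be meant only for the map analyses, and a condensed article may leave the definition of the region to a fuller document.

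Part of this stands. A reader might infer that the lesion-perfusion expectation has no valid test at all. The article does not support that: a lesion region may be intended, and low power at some assumed overlaps does not make a test invalid. What remains is that the significance rule is written to cover any difference among the conditions, is set at the voxel level, and is the only one given for imaging. Followed literally, it does not match the stated target. That is a matter of what the text fixes, not of detail left out.

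The power figures also have clear limits. Overlap, effect size and the absence of an effect outside the lesion are all assumed. Aphasia-causing lesions may overlap substantially. A cluster analysis searches the whole map, including the voxels of greatest overlap, so power at one voxel is not the power of the full analysis. A mask mean need not have the same standardised effect as a voxel. The figures show direction and a plausible range; they do not show that a real gain would probably be missed.

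Finally, the remark in the Introduction, "Given the variability in lesion location and size", is general background on choosing a cortical stimulation site. The inclusion criteria are the better basis for expecting lesions in different places in this trial.

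**Conclusion.** The point holds as a mismatch between target and stated rule. A voxelwise group test does not estimate change in each patient's own lesion, and it is less sensitive to such change whenever lesions overlap incompletely and the effect is concentrated in the lesion. The first part follows from the text alone and needs no power assumption. The size of the second cannot be fixed from the article. Under the assumptions above, single-voxel power ranges from 68% at 80% overlap to 9% at 20%, with 33% at 50% and 15% at 30%, against 86% for a lesion-mask mean.

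The consequence is limited. Perfusion is one strand of the secondary imaging outcomes, the claim at issue is an anticipation in the Discussion, and the primary WAB comparison is untouched. It is a desirable improvement, not a flaw that threatens the trial.

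**What to change.** In Imaging data analysis, add for the lesion-perfusion question:

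- One value per patient and visit: mean ASL blood flow within that patient's own T0 lesion mask.
- Comparison of real with sham at each follow-up, adjusted for the T0 value.
- The voxelwise ASL analysis kept as exploratory, with the voxel and cluster threshold applying to that map analysis.

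If a regional lesion analysis is already intended, one sentence saying so is enough.

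Expressing lesion flow relative to the mirror region in the right hemisphere should be a sensitivity analysis at most. The Introduction says that the right hemisphere may compensate during language recovery, so flow there could itself change and either hide or create a difference between arms.

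The cost is small: the scans and lesion extraction are already planned, and only one summary value per patient and visit is added. The downside is that averaging over the mask hides variation within the lesion.

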## Methods

### Study design

This is a randomized, double-blinded, sham-controlled and single-center clinical study (Registry: Chinese Clinical Trial Registry; Registration number: ChiCTR2600125453). Patient with PSA will be recruited and will be randomized 1:1 into two groups: the sham and real stimulation group. Patient in the real stimulation group will receive rTMS targeting the right cerebellum, as well as conventional language rehabilitation training. While the sham stimulation will be implemented in the sham group. Language and cognitive function evaluation and neuroimaging data will be collected before rTMS treatment (T0) and at 2 weeks (T1), 3 months (T2), 6 months (T3), and 1 year (T4) after treatment (Please see more details in Fig 1 and Fig 2). The trial protocol conforms to the Standard Protocol Items: Recommendations for Interventional Trials (SPIRIT) Checklist (S1 Checklist) [40]. All participants have provided signed informed consent (S2 File). The study will adhere to the guidelines set forth in the Declaration of Helsinki.

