### Statistical analysis

#### Behavior data analysis.

SPSS 26.0 statistical software will be used to analyze behavior data (the performance of scale assessment which mentioned above). We will use the Intention-to-treat analysis in this study. Shapiro-Wilk test will be used to verify whether the data are normally distributed. For normally distributed measures, t-test and repeated-measures analysis of variances will be used to compare the behavior functions between the same group before and after treatment and between the real and sham rTMS group in the same phase. For non-normally distributed measures, the Mann-Whitney U Test and Kruskal-Wallis H test will be used for comparison across the conditions. P-value < 0.05 is considered significant (two-tailed).

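### The one-way ANOVA named for imaging treats repeated scans as independent and states no comparison of change between real and sham rTMS

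*Protocol article*

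**What the plan says.** Under Imaging data analysis, the protocol article names the test: "One-way ANOVA will be performed to compare the imaging parameters among the groups (pre-vs. post-treatment, real vs. sham treatment". For DTI, differences in the cerebral-cerebellar loop "will be identified between different groups and pre-/post treatment using Tract-Based Spatial Statistics (TBSS) analysis". The processed DTI, rs-fMRI and ASL data "will be employed to evaluate cerebellar stimulation’s effect on aphasia recovery in terms of structure, function, and perfusion".

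The Study design section gives the scan schedule: "neuroimaging data will be collected before rTMS treatment (T0) and at 2 weeks (T1), 3 months (T2), 6 months (T3), and 1 year (T4"). Each patient is therefore scanned repeatedly. The abstract defines the outcome as a change: "Secondary outcomes include alterations in the structure, function, and perfusion neuroimaging data". It also says the trial will show whether stimulation "strengthens the functional connection of the cerebro-cerebellar network".

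For the scales, Behavior data analysis names a different method: "t-test and repeated-measures analysis of variances will be used to compare the behavior functions". The imaging section has no counterpart. It names no paired model, change score, subject factor or group-by-time term.

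**The concern.** The bracket in the imaging sentence lists two factors. Pre/post is within patient and real/sham is between patients. A one-way ANOVA has a single factor and assumes independent observations, so it matches neither the pairing nor the crossing. This is a named method that does not fit the design, not a detail left for an analysis plan.

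Both arms receive speech-language therapy, and the Trial innovation section describes the subacute phase as a period of high plasticity in which brain activation shifts over weeks to months. Change shared by both arms is therefore to be expected. The imaging section counts any difference among the conditions as significant once it passes the threshold. A shared recovery change could then be reported as an effect of stimulation, while a true difference in change would be judged against the wrong error.

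**Working it through.** **The plan's own figure.** The Sample size section gives d = 0.86, two-sided alpha 0.05, power 90% and 1:1 allocation. A two-sample t-test (noncentral t) needs 30 per group (power 90.6%; 29 per group gives 89.6%), so 60 in total, and 60 × 1.1 = 66. The figure reproduces and is not in dispute. The checks below use its 30 evaluable patients per arm.

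**Assumptions not in the documents.** One region-level measure with SD 1, one pre and one post scan, no voxelwise correction, pre/post correlation r from 0 to 0.9, and changes of 0.5 SD.

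**Reading A: one four-cell ANOVA (real-pre, real-post, sham-pre, sham-post).** Let both arms change by 0.5 SD, with no treatment effect. The cell means are 0, 0.5, 0, 0.5 around a grand mean of 0.25. At r = 0 the noncentrality is 30 × 4 × 0.25² = 7.5 on F(3, 116), which gives 61% rejection. Simulation over r = 0 to 0.9 gives 61-65%. The between-arm test of change rejects 5% at every r.

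**Reading B: pre versus post, and separately real versus sham.**
- Post-treatment real versus sham, same scenario: about 5% rejection at every r. It is a valid randomised comparison.
- Unpaired pre versus post with no change at all: the model takes the variance of the mean difference as 2/30, whereas the true value is 2(1 − r)/30. The test is therefore too conservative whenever r > 0 (table, second column).

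**Same contrast, two error terms.** Let the arms differ in change by 0.5 SD. The true standard error of the difference in change is √(4(1 − r)/30). An independent-scan model uses √(4/30) = 0.365 whatever r is.

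| r | Unpaired pre/post, rejection under no change | True SE | Power, independent-scan error | Power, paired error |
|---|---|---|---|---|
| 0 | 5% | 0.365 | 27% | 27% |
| 0.3 | 2% | 0.306 | 24% | 36% |
| 0.5 | 0.7% | 0.258 | 20% | 48% |
| 0.7 | 0.1% | 0.200 | 14% | 69% |
| 0.9 | about 0% | 0.115 | 5% | 99% |

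Example at r = 0.7. With the paired error the noncentrality is 0.5/0.200 = 2.5 on 58 df, giving 69%. With the independent-scan error the estimate must exceed 1.981 × 0.365 = 0.723. That is (0.723 − 0.5)/0.200 = 1.1 true standard errors above the expected value, or about 13% by normal approximation, against 14-15% in simulation. Simulated entries carry an error of up to about one percentage point.

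**Overall F against the targeted test.** When only the real arm changes, by 0.5 SD, the four-cell F rejects 47 / 45 / 43 / 40 / 36% at r = 0 / 0.3 / 0.5 / 0.7 / 0.9, against 27 / 36 / 48 / 69 / 99% for the test of change. The ordering depends on r.

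**The case against.** The strongest defence is that the bracket may list two separate comparisons. On that reading the real-versus-sham comparison after treatment is protected by randomisation and keeps its 5% level. This stands, and it rules out a reading a reader might reach: that a group-by-time term is the only contrast able to answer the treatment question. What remains on this reading is an unused baseline and an unpaired pre/post test.

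Three other stronger readings are tempting and are not supported.
- The 60-65% is not a false-positive rate. In that scenario the cells truly differ, and the F test detects it correctly. The error arises only if the result is read as a treatment effect. The article does not say it will be read so, nor which contrasts follow.
- Ignoring the pairing does not inflate type I error here. With positive correlation it makes the pre/post and interaction tests conservative. Nor is the four-cell F always less powerful than a test of change: at low correlation it rejects more often, though without isolating the treatment contrast.
- It goes too far to say that the mechanistic aim is left unanswered. The Introduction words it as to "examine alterations in functional connectivity between the cerebellum and language-related cortical regions pre- and post-treatment", which a pre/post comparison addresses in part. The stimulation-specific question comes from the abstract and the imaging section.

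An interaction contrast could also be built on a four-cell model. None is stated, and its independent-scan error would still be wrong.

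**Conclusion.** The point holds. The named test does not fit repeated scans in two arms, and no comparison of change between arms is stated, although the imaging data are meant to show what stimulation does. On the four-cell reading, a significant result is not evidence that real rTMS outperformed sham. On the two-comparison reading, the between-arm test is valid but inefficiently specified, and the pre/post test is over-conservative. On either reading, a contrast of change scored with independent-scan error loses power at any positive correlation.

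The percentages rest on assumed correlations and a 0.5 SD change in a single region-level measure. They show direction and rough size and do not carry over directly to voxelwise maps with cluster correction. Whether the ANOVA also covers DTI, which is assigned to TBSS, is unclear. Imaging is a secondary outcome, so this should be corrected, but it does not affect the sample size or the primary West Aphasia Battery analysis.

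**What to change.** Replace the one-way ANOVA sentence. For each imaging parameter, specify a between-arm comparison that uses the within-patient structure:
- a two-sample comparison of post-minus-pre change maps, or of post-treatment values adjusted for the baseline value; or
- a subject-level group-by-time factorial in SPM12, which is already the named software.

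Baseline adjustment is the safer choice if scan-to-scan correlation may be low. Its residual variance is about 1 − r² per patient, against 2(1 − r) for a change score. Since 1 − r² = (1 − r)(1 + r), it is never the larger of the two.

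State that treatment claims rest on this comparison and that within-arm pre/post results are descriptive. Apply the same rule to the TBSS comparison, and say whether the general test covers DTI.

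The cost is analysis wording and a different design matrix. No new scans or patients are needed. By the Trial status section recruitment is expected to run to December 2028, so the change can be made well before analysis.
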